## Materials and methods

Study design

The ADD-ARNI study (trial registration number: CTRI/2024/07/071165) is a prospective, multicenter, observational study being conducted at 200 sites across India from September 2024 and is expected to be completed by June 2025. The primary objective of this study is to assess the dosage pattern and treatment persistence of ARNI therapy in patients with HFrEF in India. The secondary objectives are to describe the medication dosage pattern and the implementation of GDMT in patients with HFrEF initiated on ARNI therapy and to evaluate its safety and effectiveness. This study was approved by the Suraksha Institutional Ethics Committee (approval number: N/A) and is being conducted in accordance with the principles of the Declaration of Helsinki, Indian Council of Medical Research (ICMR), International Conference on Harmonization (ICH), Good Clinical Practice (GCP) guidelines, and applicable legislations. The overall study design of the ADD-ARNI study is depicted in Figure 1.

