**Figure 1 FIG1:**
[figure not shown]
Flowchart of the study ARNI: angiotensin receptor-neprilysin inhibitor; GDMT: guideline-directed medical therapy; NT-proBNP: N-terminal pro-B-type natriuretic peptide; NYHA: New York Heart Association Original figures are created by the authors and are not adapted from any other sources.

Study population

The study population will consist of symptomatic chronic HFrEF patients as per the European Society of Cardiology (ESC) 2016 criteria [22] and who are eligible for the initiation of sacubitril/valsartan tablets as per the judgement of the treating physician. Patients who are recently diagnosed with HFrEF or chronic HFrEF patients with left ventricular ejection fraction (LVEF) ≤40% and documented for not more than three months, who are stable, and who have not been hospitalized for the past one month prior to enrolment in the study shall be included. Written informed consent shall be obtained from all participants prior to their inclusion in the study. Patients who were deemed ineligible included pregnant and lactating women, patients with acute decompensated HF, patients with hyperkalemia (serum potassium level ≥5.30 mmol/L) within the past two weeks, and patients participating in any other clinical study. Patients should meet all the inclusion criteria and none of the exclusion criteria prior to being enrolled in the study.

Study treatment, duration, and endpoints

Study participants who meet all the inclusion criteria and are deemed eligible for the initiation of ARNI therapy as per the clinical judgement of the treating physician will be initiated on ARNI therapy as per routine clinical practice. This is an observational study that will be conducted over a period of 12 weeks±4 weeks from the date of enrolment of the patient.

The primary endpoint of the study is the dosage pattern of ARNI at the start and end of the study. The secondary endpoints include the HFrEF medication dosing pattern at the start and end of the study with regard to the doses of BB, MRA, SGLT2i, and diuretics, the implementation of GDMT at the end of the study, the assessment of the effectiveness of ARNI therapy based on changes in New York Heart Association (NYHA) functional class and N-terminal pro-B-type natriuretic peptide (NT-proBNP) levels from baseline to follow-up, and the incidence of adverse events, either spontaneously reported by the patients or noticed by the clinician during the study.

Data collection

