All data required to fulfill the primary and secondary objectives of the study will be captured in an electronic data capture platform. The data related to demographic and clinical characteristics of patients will be collected at baseline. Additionally, the data points with respect to clinical parameters such as vitals, estimated glomerular filtration rate (eGFR), serum creatinine, serum potassium, and NT-proBNP will be recorded at baseline. Medication-related data, including type of medications, dosage, and titration, will be recorded at baseline and at the end of 12±4 weeks. Any incidences of adverse events will be documented during the study period.

Safety reporting

All adverse events will be captured starting from the date of enrolment until the end of the study, regardless of whether or not they are related to the study intervention. Adverse events, not limited to symptomatic hypotension (systolic blood pressure (SBP) ≤100 mmHg with symptoms like dizziness, blurry vision, fainting, fatigue, and unsteadiness), asymptomatic hypotension (SBP ≤90 mmHg with no symptoms), hyperkalemia (serum potassium levels >5.5 mmol/L), impaired renal function (decline in the eGFR of ≥50%), and persistent cough, shall be recorded during follow-up visits along with any additional adverse events [14]. It is the responsibility of the investigator to capture and report the adverse events (serious and non-serious).

Sample size calculation

The list of potential demographic and clinical characteristics, along with the distributions of patients with HFrEF, was extracted from Philip et al. [23] and Pokharel et al. [24]. Expecting a similar distribution of these characteristics in the current study, the minimum required sample sizes were calculated for 5%, 3%, and 2% precision with a 95% confidence interval (CI). In this study, the target patient population is 3,000, and accounting for an estimated ~15% attrition rate, the sample size is set at 3,600.

The following formulas were used for sample size calculation: for prevalence, \begin{document}n=\frac{\left(1.96\right)^{2}p\left(1-p\right)}{d^{2}}\end{document}, while for mean, \begin{document}n=\frac{\left(1.96xSD\right)^{2}}{d^{2}}\end{document}. Here, p means proportion or prevalence; SD, standard deviation; and d, precision. For proportion, d is absolute, but for mean, it is relative to the mean.

Statistical consideration

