All statistical tests will be performed using appropriate software, with a two-tailed overall significance level of 0.05. Categorical data (counts and percentages) will be compared between baseline and 12 weeks using the chi-squared test (or any other test deemed appropriate), while numerical data will be compared between the two groups using an unpaired t-test (or any other test deemed appropriate).

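### The named default tests for baseline versus 12 weeks assume independent samples, but the same patients are measured at both times; the clause allowing another test does not correct the default.

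*Protocol article*

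**What the plan says.** The Study design section describes a single cohort: the study "is a prospective, multicenter, observational study being conducted at 200 sites across India". No comparison arm is defined anywhere in the article.

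The endpoints compare two time points in that cohort. Under Study treatment, duration, and endpoints: "The primary endpoint of the study is the dosage pattern of ARNI at the start and end of the study". Secondary endpoints include doses of other heart failure drugs at start and end, and change in NYHA class and NT-proBNP from baseline to follow-up. Under Data collection, medication data "will be recorded at baseline and at the end of 12±4 weeks".

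The Statistical consideration section sets tests "with a two-tailed overall significance level of 0.05". For categorical data: "Categorical data (counts and percentages) will be compared between baseline and 12 weeks using the chi-squared test (or any other test deemed appropriate"). For numerical data: "numerical data will be compared between the two groups using an unpaired t-test", followed by the same bracketed clause allowing another test. No paired method is named. The section does not say whether patients without a follow-up value contribute their baseline value to these comparisons.

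**The concern.** With one cohort and no second arm, the groups in the t-test sentence can only be the two time points. Each patient then supplies a value to both, and the two values are usually positively correlated. The chi-squared test and the unpaired t-test take them as independent.

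Two consequences follow, by different routes:

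- **Complete pairs.** The standard error of the change is overstated. Intervals are too wide, tests reject too rarely, and power is lost. The error is conservative.
- **Incomplete pairs.** An unpaired test does not require both values from a patient. All baseline values can therefore be set against follow-up values from the patients who remain. If those who leave were sicker at baseline, the average falls between the two time points although no patient changed. This error can produce a false finding of improvement.

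At stake are the tests and intervals for change in ARNI dose, other drug doses, NYHA class and NT-proBNP. The last two are the study's evidence on effectiveness.

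**Working it through.** **Inputs from the article.** One cohort measured twice; two-sided 0.05; target 3,000, attrition of about 15%, sample size set at 3,600.

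**Inputs assumed.** The article gives no within-patient correlation, so ρ = 0.3, 0.5 and 0.7 are used. It gives no baseline difference between leavers and completers, so 0.3, 0.4 and 0.5 SD are used. Equal SD at both times is assumed.

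**The plan's own figure.** 3,000 / (1 − 0.15) = 3,530, which is 1.9% below 3,600. Exactly 3,600 corresponds to 1 − 3,000/3,600 = 16.7% attrition. The stated number is compatible with attrition of about 15% and is not affected by this point.

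**Step 1: width of the interval.** For n complete pairs, the true variance of the mean difference is 2·SD²·(1 − ρ)/n. The unpaired t-test uses 2·SD²/n. The ratio of standard errors is 1/√(1 − ρ).

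**Step 2: true type I error.** The unpaired statistic has variance 1 − ρ under no change, so the true level is 2·[1 − Φ(1.96/√(1 − ρ))].

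**Step 3: power.** Take the change that a paired test detects with 80% power, which is 1.96 + 0.84 = 2.80 paired standard errors. The unpaired test rejects with probability P(Z > 1.96/√(1 − ρ) − 2.80). At ρ = 0.7 this is P(Z > 3.58 − 2.80) = P(Z > 0.78) = 22%.

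| Assumed ρ | Interval too wide by | True level at nominal 0.05 | Power where paired has 80% | Half-width, 3,000 pairs: unpaired → paired |
|---|---|---|---|---|
| 0.3 | 1.20 | 0.019 | 68% | 0.051 → 0.042 SD |
| 0.5 | 1.41 | 0.006 | 51% | 0.051 → 0.036 SD |
| 0.7 | 1.83 | 0.0004 | 22% | 0.051 → 0.028 SD |

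**Step 4: categorical data.** In 4,000 simulated studies of 3,000 pairs with no change, a binary item was formed by cutting a correlated latent variable. The chi-squared test rejected in 1.5% (latent ρ = 0.5) and 0.5% (latent ρ = 0.7) of runs. McNemar's test rejected in 4.7% and 5.1%.

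**Step 5: attrition, on the condition that all baseline values are used.** With 15% leaving, 3,600 × 0.85 = 3,060 remain. If leavers are k SD worse at baseline and nobody changes, the apparent improvement is 0.15·k SD. The unpaired SE is √(1/3,600 + 1/3,060) = 0.0246 SD.

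| Assumed k | Apparent improvement | Expected z | p at that z |
|---|---|---|---|
| 0.3 | 0.045 SD | 1.83 | 0.067 |
| 0.4 | 0.060 SD | 2.44 | 0.015 |
| 0.5 | 0.075 SD | 3.05 | 0.002 |

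A binary illustration, also with assumed rates: if 35% of completers and 55% of leavers are in NYHA class III/IV at baseline, the baseline figure is (3,060 × 0.35 + 540 × 0.55)/3,600 = 38%. The follow-up figure is 35% with no patient changing, and the chi-squared test gives z = 2.53, p = 0.011.

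**The case against.** **The clause allows a paired test.** It is attached to both named tests and would admit McNemar's test or a paired t-test. The choice may already be fixed in an analysis plan that is not shown. This stands in part. A reader might infer that every start-versus-end comparison will be wrong, or that the alternative will be picked after the data are seen. The article supports neither: comparisons are affected only if the named defaults are used, and nothing is said about when an alternative would be chosen. But the clause does not turn an independent-sample default into a suitable one.

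**The dropout route is not in the text.** A reader might infer that the plan compares all enrolled patients with completers. It does not say so. An unpaired test can be run on completers only, and inflating a target of 3,000 to 3,600 fits an analysis of roughly 3,000 followed patients. This stands, so the attrition result is conditional. It also depends on the assumed gap: at 0.3 SD the expected p is above 0.05.

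**The direct error is conservative and small in absolute terms.** With 3,000 pairs the unpaired half-width is only 0.051 SD, and the changes for which paired power is 80% are themselves small: at ρ = 0.7, 2.80 × √(2 × 0.3/3,000) = 0.040 SD. Larger changes would be detected either way. This stands for complete pairs.

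**The primary endpoint is descriptive, and sample size rests on precision.** This also stands. Percentages at each dose at start and end are valid marginal descriptions. GDMT implementation at study end and adverse events are not before/after comparisons.

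**Conclusion.** The point holds in limited form: the article names tests for independent samples for data that its own design makes paired. That is a wrong statement, not a detail left to another document.

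If the defaults are used on complete pairs, the cost is lost precision and power, as tabulated for assumed correlations of 0.3 to 0.7, with a true level below 0.05. On complete pairs the defaults do not raise the false-positive rate, so a claim that they do would be unsupported.

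False improvement needs two further conditions: all baseline values enter the comparison, and leavers were worse at baseline. The article neither states nor excludes the first and gives no figure for the second.

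A reader might also conclude that the dosage-pattern results are invalid. They are not; only tests and intervals for change are affected. Nor can the loss for NT-proBNP or multi-level dose be given a specific size, because the article gives no distribution, correlation or expected change for either.

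**What to change.** Replace the sentence on tests with paired defaults, for patients with values at both times:

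- **ARNI dose level and NYHA class:** a baseline-by-follow-up shift table, with a Stuart-Maxwell or Wilcoxon signed-rank test.
- **Binary items, such as being on or off a drug class:** McNemar's test, with a confidence interval for the paired difference.
- **Numerical data:** a paired t-test with a confidence interval for the mean change; for NT-proBNP, on the log scale if the values are skewed.

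State explicitly that before/after comparisons use patients with both values. Tabulate baseline values of completers beside those of non-completers. Pairing confines the estimate to completers but does not remove selection by dropout, so readers need to see how the two differ. If the clause allowing another test is kept, say that any alternative must also respect the pairing.

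The cost is a few lines of analysis wording. No extra data or patients are needed, and the sample size is unchanged.

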## Results

The expected results of the study will include the dosage pattern of ARNI therapy at both the start and end of the study, the dosing patterns of other HFrEF medications, the implementation of GDMT, and the effectiveness of ARNI therapy as assessed by changes in NYHA functional class and NT-proBNP levels from baseline to follow-up. Additionally, the incidence of adverse events will be recorded.

## Discussion

The primary objective of HF treatment is to effectively prevent complications while ensuring prolonged survival, free from morbidity [11]. ADD-ARNI is the first-of-its-kind prospective, multicenter observational study designed to assess the dosage patterns and treatment persistence of ARNI therapy in patients with HFrEF in India. This study also seeks to analyze the implementation of GDMT, the effectiveness of ARNI therapy in terms of changes in NYHA functional class and NT-proBNP levels, functional improvements, and adverse events. These findings are expected to provide insights into the real-world use of ARNI and its impact on HF management in the Indian population.

Data from Indian HF registries suggest a relatively higher prevalence of HFrEF (Table 1) [2,8-10,18].

**Table 1 TAB1:** Trends in Indian HF-EF distribution N=total number of patients for each registry CSI-Kerala: Cardiology Society of India-Kerala Acute Heart Failure Registry; ICC-NHFR: Indian College of Cardiology National Heart Failure Registry; ICMR-NHFR: Indian Council of Medical Research National Heart Failure Registry; THFR: Trivandrum Heart Failure Registry; HFrEF: heart failure with reduced ejection fraction; LVEF: left ventricular ejection fraction; HFpEF: heart failure with preserved ejection fraction; HFmEF: heart failure with mildly reduced ejection fraction; HFrEF: heart failure with reduced ejection fraction The data for HFpEF and HFmEF from the Medanta and ICC-NHFR registries have been presented in a combined format, as reported in the original sources.

Registry	HFrEF	HFpEF	HFmEF
THFR (n=1205) [18]	62%	20%	18%
CSI-Kerala (n=7507) [9]	65.7%	14.9%	17.6%
Medanta (n=5590) [8]	59.1% (LVEF ≤30%)	41.9% (LVEF ≥30%)	
ICC-NHFR (n=5269) [10]	68.29% (LVEF <40%)	31.7 1 (LVEF >40%)	
ICMR-NHFR (n=10851) [2]	65.2%	12.6%	22%

HFrEF poses a significant public health challenge due to its associated high morbidity and mortality rates [25]. In India, the one-year mortality rate is relatively higher at 31% compared to other Asian countries (Figure 2) [8,10,18,26-29].

**Figure 2 FIG2:**
[figure not shown]
One-year mortality rates in Asia N=total number of patients for each registry Asian HF: Asian heart failure [28]; ICC-NHFR: Indian College of Cardiology National Heart Failure Registry [10]; Korea HF: Korea heart failure [29]; Medanta HF: Medanta heart failure [8]; THAI-AHF: Thailand-acute heart failure [26]; THFR: Trivandrum Heart Failure Registry [18]; TSOC-HFrEF: Taiwan Society of Cardiology-heart failure with reduced ejection fraction [27] Original figures are created by the authors and are not adapted from any other sources.

For patients with HFrEF, adhering to guideline-recommended therapies and ensuring up-titration to evidence-based doses is a proven strategy to deliver optimal care. This approach plays a critical role in reducing the risk of recurrent HF hospitalizations and cardiovascular mortality [16,30]. The present study will assess persistence with ARNI therapy over a 12-week period, explore the titration to target doses, and identify barriers to achieving these targets.

Evidence from previous studies, such as the CHAMP-HF Registry, evaluated the effectiveness of medical therapy dosing for HF in outpatients with chronic HFrEF. The study found that compared to target dosing, lower dosages and non-use of ACEI/ARB/ARNI and beta-blocker therapies were independently associated with higher mortality rates. Additionally, lower doses of ACEIs/ARBs/ARNIs were associated with an increased risk of HF hospitalizations and a higher five-year mortality [17].

The secondary objective of the present study will be to evaluate the implementation of GDMT at the end of the study, expressed as the proportion of patients on two, three, or four GDMT drugs. Previous studies, including the ICMR-NHFR study, reported that nearly one in two eligible patients with HF received GDMT. The importance of GDMT lies in its association with improved survival rates for patients with HFrEF and heart failure with mildly reduced ejection fraction (HFmrEF). In contrast, those with HFrEF and HFmrEF who did not receive GDMT experienced higher mortality rates, underlining the critical role of GDMT in improving outcomes. The overall 90-day mortality rate for these patients was reported as 14.2% [2]. Furthermore, the Trivandrum Heart Failure Registry has highlighted significant gaps in the implementation of GDMT, despite its proven association with reduced mortality and improved survival. In the Trivandrum Heart Failure Registry, for instance, only one in six patients received guideline-based in-hospital treatment, which was associated with improved survival rates and lower mortality [7]. The present study aims to explore whether similar trends exist in its cohort, contributing further insights into the gaps in GDMT adherence. Additionally, data from the CSI-KHFR provide further evidence of suboptimal GDMT implementation, as only one in four patients received guideline-based treatment (Figure 3).

**Figure 3 FIG3:**
[figure not shown]
Implementation of GDMT in India N=total number of patients for each registry CSI-Kerala: Cardiology Society of India-Kerala Acute Heart Failure Registry [9]; GDMT: guideline-directed medical therapy; ICC-NHFR: Indian College of Cardiology National Heart Failure Registry [10]; ICMR-NHFR: Indian Council of Medical Research National Heart Failure Registry [2]; THFR: Trivandrum Heart Failure Registry [18] Original figures are created by the authors and are not adapted from any other sources.

The CSI-KHFR also reported an in-hospital mortality rate of 7% and a 90-day mortality rate of 11.6% [9]. These findings highlight the critical need for improving GDMT adherence in the management of HF in India.

In the present study, the effectiveness of ARNI therapy will be evaluated based on changes in NYHA functional class and NT-proBNP levels from baseline to follow-up. Previous findings suggest that improvement in the NYHA class is associated with a lower risk of all-cause and cardiovascular mortality, as well as a reduced likelihood of first HF hospitalization [31]. Furthermore, another study reported that lower NT-proBNP levels are associated with a reduced six-month all-cause mortality rate [32].

Previous studies have demonstrated the efficacy of ARNI in improving both NYHA class and NT-proBNP levels [33-35]. The PARADIGM-HF India sub-study specifically highlighted the effectiveness of ARNI in improving NYHA class compared to enalapril [33]. Similarly, a single-center, open-label observational registry of consecutive HF patients initiated on ARNI at the National Heart Centre Singapore found that ARNI resulted in improvements in both NYHA class and NT-proBNP levels at three months compared to baseline and was generally well-tolerated [34]. The PROVE-HF trial, a prospective study of biomarkers, symptom improvement, and ventricular remodeling during sacubitril-valsartan therapy for HF, found that patients with HFrEF treated with sacubitril-valsartan experienced a rapid reduction in NT-proBNP, a well-established biomarker for HF severity and prognosis. This reduction was weakly but significantly correlated with improvements in markers of cardiac volume and function at 12 months, suggesting reverse cardiac remodeling after one year [35].

Despite the growing body of evidence supporting the benefits of sacubitril-valsartan therapy in clinical trials, there remains a paucity of real-world data regarding its use, the utilization of GDMT, and insights from clinical experience in India, particularly concerning the characteristics of HFrEF patients treated in routine clinical practice. This lack of data is especially concerning given the unique demographic and clinical characteristics of the Indian population, which could influence treatment outcomes. Therefore, a real-world study is essential to evaluate the use of sacubitril-valsartan therapy and the optimal implementation of GDMT in India. The ADD-ARNI study seeks to bridge this gap by providing evidence-based insights into the effectiveness of ARNI therapy in an Indian cohort. The findings of this study could significantly impact clinical decision-making, ultimately helping to optimize treatment strategies and improve patient outcomes in India.

The present study will also monitor adverse events associated with ARNI therapy, either spontaneously reported by patients or identified by clinicians. The PARADIGM-HF India sub-study reported that the most common adverse events (>10%) were cough, hyperkalemia, hypotension, and dyspnea [33]. Likewise, a retrospective cohort study conducted by Koçak et al. reported that hypotension was the most frequently observed adverse event, affecting 16% of patients with HF initiated on sacubitril-valsartan; among these, 4% were symptomatic [36]. A previous real-world study in India included patients aged ≥18 years with HFrEF (LVEF <40%) who were prescribed sacubitril-valsartan, assessing its dose titration over six months [37]. In contrast, the present study will evaluate the overall dosage patterns of ARNI therapy and the implementation of GDMT for HF, aiming to provide a broader perspective on real-world practice in India.

Strengths and limitations

This study has several notable strengths. ADD-ARNI is the first-of-its-kind prospective, multicenter observational study designed to assess the dosage patterns and treatment persistence of ARNI therapy specifically in patients with HFrEF in India. By including a substantial HFrEF population, the study ensures a more comprehensive representation of patients across diverse real-world settings. Furthermore, it addresses the existing gap in literature by providing evidence on the effectiveness of ARNI therapy in an Indian cohort, a population in which limited real-world studies have been conducted. Additionally, this study will provide valuable insights into dosage patterns, treatment persistence, and the implementation of GDMT in patients with HFrEF initiated on ARNI therapy, providing practical data to inform clinical decision-making.

Despite its strengths, the study has some limitations. The shorter duration of 12 weeks may not be sufficient to capture long-term treatment persistence, adherence, and outcomes associated with ARNI therapy. While a longer duration could have provided more robust data on the sustained effectiveness and safety of ARNI therapy, it also comes with certain constraints, such as increased resource requirements and logistical challenges. Therefore, the present study opted for a shorter duration to ensure feasibility and timely completion. Additionally, as a non-randomized, real-world study, it is inherently prone to bias, which could influence the results. Factors such as variations in clinician practices, patient characteristics, and adherence to therapy may contribute to this bias. By acknowledging these limitations, the study highlights areas for future research to build upon its findings.

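### The before-after change in NYHA class and NT-proBNP is labelled as the effectiveness of ARNI, although the design has no comparator and other heart failure drugs may change over the same weeks

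*Protocol article*

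**What the plan says.** All references are to the Protocol article.

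- **Design.** Under Study design, ADD-ARNI "is a prospective, multicenter, observational study being conducted at 200 sites across India". Evaluating the effectiveness of ARNI is part of the secondary objectives there.
- **Exposure and follow-up.** Under Study treatment, duration, and endpoints, eligible participants "will be initiated on ARNI therapy as per routine clinical practice", and the study is "conducted over a period of 12 weeks±4 weeks from the date of enrolment of the patient". No untreated or differently treated group is described.
- **Endpoint.** The same section lists as a secondary endpoint "the assessment of the effectiveness of ARNI therapy based on changes in New York Heart Association (NYHA) functional class" and NT-proBNP. The Results and Discussion repeat it; the Discussion says that "the effectiveness of ARNI therapy will be evaluated based on changes in NYHA functional class and NT-proBNP levels from baseline to follow-up".
- **Co-medication.** Another secondary endpoint is the dosing pattern at start and end "with regard to the doses of BB, MRA, SGLT2i, and diuretics". Data collection adds that titration is recorded.
- **Intended conclusion.** The Discussion presents the study as "providing evidence-based insights into the effectiveness of ARNI therapy in an Indian cohort". Strengths and limitations counts this among the strengths, and Conclusions repeats it.
- **Caveat.** Strengths and limitations concedes that "as a non-randomized, real-world study, it is inherently prone to bias" and names clinician practice, patient characteristics and adherence as sources.

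**The concern.** Effectiveness of a named drug is a causal statement: it says what the drug contributed beyond what would have happened without it. A single-arm change from baseline contains that contribution plus everything else that moved in the interval. Here the rest may include starts or dose changes of four other drug classes, natural change in recently diagnosed or recently documented disease, some regression to the mean, and the influence of open treatment on a functional class that calls for judgement.

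At stake is the meaning of a secondary result that the article expects to inform clinical decisions. A reader of the final report could credit to ARNI an improvement that came partly or wholly from other causes, and nothing in the design would reveal it.

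**Working it through.** **1. What the stated comparison can identify.** Write the mean change as

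observed change = ARNI effect + effect of other drug changes + natural change over time (including any regression to the mean) + assessment effects.

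With all patients on ARNI and no comparator, only the sum on the left is observed. The Statistical consideration section compares baseline with 12 weeks; that tests whether the sum is zero, not whether the first term is.

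**2. Whether the article itself makes the other terms plausible.**
- *Other drugs:* their doses are measured at start and end as an endpoint, so the plan allows for change. The Introduction credits the GDMT classes together, not ARNI alone, with better cardiac function and functional status.
- *Time:* Study population admits recently diagnosed patients, or chronic patients with LVEF ≤40% documented for at most three months.
- *Assessment:* treatment is open, so NYHA class is not assessed blind to it.

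**3. Contrast within the Discussion.** It cites an Indian sub-study in which ARNI improved NYHA class compared with enalapril, which is a controlled comparison. It also cites a single-centre registry with improvement from baseline only. ADD-ARNI has the second design and claims the first kind of inference.

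**4. Does the large sample help?** The article's only related figure is the sample size: 3,000/(1 − 0.15) = 3,530, close to the stated 3,600 (which implies 1 − 3,000/3,600 = 16.7% attrition). It is based on precision and gives no effect size or SD for NYHA class or NT-proBNP, so what follows is illustration.

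Assume no ARNI effect, n = 3,000 completers and two-sided alpha 0.05. Let other causes shift the mean by b.

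- Paired test, b in SDs of the change: P(significant) = 1 − Φ(1.96 − b√3000) + Φ(−1.96 − b√3000), with √3000 = 54.77.
- Unpaired test, as named in Statistical consideration, b in SDs of the measurement, assumed within-patient correlation 0.5: the test uses SE √(2/3000) = 0.0258, while the true SE is √(2 × 0.5/3000) = 0.0183.

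| b | Paired | Unpaired |
|---|---|---|
| 0 | 5% | 0.6% |
| 0.02 | 19% | 4.7% |
| 0.05 | 78% | 49% |
| 0.10 | >99.9% | 99.7% |

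**5. Size of a co-medication effect on NT-proBNP.** If a share q of patients start another drug that multiplies NT-proBNP by r, the whole-cohort geometric mean ratio is r^q, with no ARNI effect. The values of q and r are assumed:

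- q = 0.1, r = 0.9: 0.99
- q = 0.3, r = 0.8: 0.94
- q = 0.5, r = 0.7: 0.84

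The range runs from negligible to substantial, and the article gives no basis for choosing within it.

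**The case against.** The strongest reply has four parts.

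- *The limitation is already admitted.* The article says the study is non-randomised and prone to bias, and names three sources. This mitigates, but it names neither the absent comparator nor co-medication change, and the effectiveness wording is left unsoftened a paragraph earlier and again in Conclusions.
- *It is only a secondary endpoint, and the article promises insights rather than a causal estimate.* It is true that the primary endpoint and the precision-based sample size are untouched. But the objective and endpoint name the effectiveness of one drug, which is a causal label however gently the conclusion is phrased.
- *The full protocol or SAP may adjust for co-medication.* It may, and the absence of adjusted or stratified tables from an article is no finding. Adjustment would still not supply a control group, and the attribution is made in the published text.
- *Entry criteria limit selection at a transient peak.* Patients must be stable, without hospitalisation in the past month and not acutely decompensated, and no NT-proBNP threshold applies. This stands. A reader might infer a sizeable regression to the mean in NT-proBNP; the usual formula assumes selection on the baseline value itself, which these criteria do not apply. It is also unclear whether the three-month limit refers to the diagnosis or to the LVEF record; on the latter reading, the argument from natural recovery weakens.

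Two further inferences go beyond the documents. A reader might suppose that the prescriber rates NYHA class; the article does not say who does, only that treatment is open. A reader might also suppose that improvement is nearly certain with 3,000 patients. Sample size makes a shift detectable but does not create one, and the table above shows near-certainty only once the non-ARNI shift is about 0.10 SD.

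**Conclusion.** The point holds as one of attribution. The design can describe how NYHA class and NT-proBNP change after ARNI is started, but it cannot show how much of that change is due to ARNI, and the article says that it will evaluate exactly that. This rests only on the article's own statements: all patients are exposed, no comparator is described, other effective drug classes may change over the same weeks, and the comparison is with baseline.

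The amount of misattribution is unknown. The figures above depend on assumed shifts, an assumed correlation and assumed drug effects; they show that a large sample is no safeguard and are not estimates for this study. Nor does the point imply that ARNI is ineffective or that the dosage-pattern results are compromised. It should be corrected before results are reported, but it does not threaten the study's main purpose.

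**What to change.** 1. Restate the secondary objective and endpoint as *change in NYHA class and NT-proBNP after ARNI initiation (descriptive, not attributed to ARNI)*.
2. Remove the claim of ARNI effectiveness from the strengths and the conclusions, and align the Abstract, Results and Discussion.
3. Name four limitations: no control group, concurrent change in other heart failure drugs, natural change over time including possible regression to the mean, and open-label NYHA assessment.
4. Optionally, describe the change separately for patients with and without a start or dose change of a beta-blocker, MRA, SGLT2i or diuretic. Label it descriptive: co-medication change occurs after initiation and may itself depend on response or tolerability, so the split does not isolate ARNI. It uses medication data already planned, but needs the follow-up NT-proBNP value, which Data collection lists only at baseline.

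The cost is mostly wording, plus one table if the option is taken. Because the study is registered, ethics-approved and under way, the reworded objective should be documented as a change. The price is a more modest claim.
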